## 4 List of Abbreviations

|              |                                                                        |
|--------------|------------------------------------------------------------------------|
| ACCP/SSCM    | American College of Chest Physicians/Society of Critical Care Medicine |
| AE           | Adverse Event                                                          |
| AKI          | Acute kidney injury                                                    |
| CIP          | Clinical Investigation Plan                                            |
| CO           | Cardiac output                                                         |
| CVP          | Central venous pressure                                                |
| CRF          | Case Report Form                                                       |
| CRRT         | Continuous Renal Replacement Therapy                                   |
| CVVH         | Continuous veno- venous hemofiltration                                 |
| CVVHD        | Continuous veno- venous haemodialysis                                  |
| CVVHDF       | Continuous veno- venous haemodiafiltration                             |
| EAA          | Endotoxin Activity Assay                                               |
| ELWI         | Extra-vascular Lung Water Index                                        |
| GCP          | Good Clinical Practices                                                |
| HMGB1        | High-Mobility Group protein B1                                         |
| HR           | Heart Rate                                                             |
| ICU          | Intensive Care Unit                                                    |
| IEC          | Independent Ethics Committee                                           |
| IL-6         | Interleukin 6                                                          |
| ISO          | International Standardization Organisation                             |
| LPS          | Lipopolysaccharide                                                     |
| MAP          | Mean arterial pressure                                                 |
| PTT          | Partial Thrombin Time                                                  |
| PVPI         | Pulmonary Vascular Permeability Index                                  |
| SOC          | Standard of Care                                                       |
| SOFA score   | Sequential Organ Failure Assessment score                              |
| TNF $\alpha$ | Tumor Necrosis Factor $\alpha$                                         |

## 5 Background

### 5.1 Identification and description of the medical device to be investigated

Septic shock has a high mortality risk despite the availability of various treatments (1). The systemic sepsis response starts with the recognition of an invading organism or its toxin.

Bacterial-associated toxins are some of the principal components of gram-negative (endotoxin) and gram-positive organisms (lipotechoic acid) (2-4).

Endotoxin, a complex lipopolysaccharide (LPS) that is present in the cell walls of gram-negative bacteria, is a potent trigger of innate immunity. The activated immune cells, principally monocytes/macrophages are able to recognize and destroy the pathogenic agents and the endotoxins by phagocytosis. These cells also release a series of mediators (cytokines) that activate other cells. Tumor necrosis factor-alpha (TNF- $\alpha$ ), Interleukin (IL-1 and IL-6) and high-mobility group box protein 1 (HMGB1), a 30 kDa alarmin, are important pro-inflammatory cytokines which activate complements and coagulation factors.

This activation of the immune cascade can lead to an overwhelming systemic overflow of pro- and anti-inflammatory mediators at the early phase of sepsis with generalized endothelial damage, tissue injury and multi-organ failure; the leading cause of death in septic patients.

#### High flow Haemofilter Device for Blood Purification

Extracorporeal blood purification therapies have been proposed for sepsis as adjuvant treatment. A recent advance in blood purification is oXiris™ (Gambro Industries, Meyzeiu, France), an extracorporeal filter capable of removing endotoxin and cytokines. The oXiris™ device contains an AN69-based membrane, which adsorbs a large spectrum of plasma cytokines, such as IL-6, IL-8, IL-10, and TNF $\alpha$ , and has the potential to reduce cytokine plasma levels (5-9). Furthermore, it has been recently demonstrated that HMGB1 can be significantly removed using a “surface-treated” version of AN69 (AN69ST) in vitro (10). The surface treatment of AN69 to produce AN69ST involves the application of a positively-charged polymer (polyethyleneimine: PEI) at relatively low concentration to the inner (blood-contacting) surface of the negatively charged AN69 membrane. Moreover, the high concentration of positive charges at the membrane inner surface allows negatively-charged bacterial products, such as endotoxin, to be adsorbed. On the other hand, this manufacturing approach has no effect on the AN69-related cytokine-adsorbing characteristics, which have been demonstrated to be preserved with oXiris™.

From an historical perspective, filters containing AN69-based membranes have been commonly used products for CRRT in the management of critically ill patients. For example, continuous veno-venous hemofiltration using the AN69 membrane has been reported to be effective in improving immune dysfunction and increasing monocyte HLA-DR expression (11). This combination of characteristics for oXiris™ potentially represents a major advantage over isolated hemoperfusion, especially regarding organ failure management during septic shock. This device is intended to be a complete blood purification option covering several aspects of the sepsis condition, including renal support for acute renal failure, a clinical entity frequently observed in septic shock patients (12). Preliminary investigations and justification of the study

#### 5.1.1 Preclinical testing

Promising in vitro and animal data have already been reported with oXiris™. In an in vitro study, bovine plasma contaminated with endotoxin from an E. coli source was circulated in a closed circuit in contact with oXiris™ at a flow rate of 250 ml/min. Sixty six per cent (66%) of the endotoxin present at the beginning of the experiment was adsorbed after a one hour treatment (13). Moreover, the use of oXiris™ during a 6-hour hemofiltration session in septic

pigs significantly improved haemodynamics as compared to pigs treated with a standard hemofiltration membrane. Interestingly, pigs that were treated with the oXiris™ membrane had serum endotoxin levels lower than pigs from the control group (13).

### 5.1.2 Previous clinical experience

Recently, an observational uncontrolled study enrolling 16 patients with severe sepsis or septic shock has shown the use of oXiris™ is associated with a significant decrease in inflammatory markers, such as procalcitonin (PCT) and interleukin 6 (IL-6). In addition, treatment with oXiris™ is associated with a significant improvement of several clinical parameters; including mean arterial pressure, norepinephrine requirements, and SOFA score (14, 15).

Hemofiltration with the oXiris™ filter is commonly performed in patients with acute renal failure and severe sepsis or septic shock, requiring CRRT.

### 5.1.3 Device risk analysis and risk assessment

The medical literature does not provide definitive information regarding the percentage of septic shock patients who develop severe acute renal failure and require renal replacement therapy. However, according to several publications based on critically ill populations with sepsis or severe sepsis, a reasonable estimate is that about 50% of patients with severe sepsis eventually require renal replacement therapy (16, 17). In the interventional group, a certain percentage of patients who do not develop acute renal failure severe enough to require renal replacement therapy will, nevertheless, receive extracorporeal therapy and be exposed to associated risks. However, morbidity specifically related to renal replacement therapy has drastically decreased over time due to improvement in machines, circuits and membranes.

In a study published by Payen et al. in 2009, the application of 'standard' continuous hemofiltration (conventional dose and filter) to a population with severe sepsis, (irrespective of the presence of renal failure), resulted in a significantly prolonged requirement for organ support (longer time to wean from mechanical ventilation and catecholamines) (17). However, the risk/benefit assessment for this study may not have been well aligned as the study assessed only a "renal support dose" rather than the potential benefits of a "sepsis modulation" blood purification therapy such as high-volume hemofiltration or high adsorption hemofiltration, which is the technique to be evaluated in the current study during a limited time period i.e. 48 hours.

In addition, all the risks related to renal replacement therapy should be viewed in the context of the potential benefits of the oXiris™ set. The oXiris™ set enables the removal of endotoxin and cytokines, compounds which are integral in the development of sepsis-related multiple organ failure.

The kinetics of endotoxin removal with extracorporeal blood purification therapy is not well described in the literature. A recent review showed conflicting results on endotoxin levels in patients treated with Polymyxin B-immobilized filters.

The rationale of the extracorporeal therapy with PMX is to remove circulating endotoxin by adsorption, thus preventing progression of the biological cascade of sepsis. Overall, nine randomized controlled trials (mainly published in Japan) investigated the PMX on outcomes (blood pressure, the use of vasoactive drugs mortality and endotoxin levels) (18-24).

Endotoxin concentrations decreased after PMX treatment in most of the studies, but did not significantly change in the European randomized controlled trial (25). A recent review reported similar adverse events, including clotting of the device when compared to CRRT

(16). Especially no adverse events indicative of nephrotoxicity and neurotoxicity were reported in a recent review (16).

The following is a list of problems that could be theoretically encountered with the use of extracorporeal blood purification treatments:

- Circuit and filter thrombosis, possibly leading to blood loss;
- Heparin-associated bleeding or heparin-induced thrombocytopenia;
- Hemodynamic instability, mainly due to hypovolemia;
- Various catheter-related complications, including inadvertent arterial puncture, local bleeding, hematoma, pneumothorax, haemothorax, retroperitoneal bleeding or cardiac arrhythmia, thrombosis, infection, mechanical problems (e.g. malpositioning);
- Electrolyte disturbances;
- Undesired losses of water-soluble compounds, including drugs and trace elements.

#### **5.1.4 Justification for the design of the clinical investigation**

Little is known about the endotoxin activity using extracorporeal blood purification. In a recent observational study of 16 patients with severe sepsis or septic shock treated with oXiris™, the authors showed a significant decrease in inflammatory markers (PCT and IL-6) and a significant improve in clinical parameters (MAP, norepinephrine requirements and SOFA score) (28). However, it is poorly described whether the hemodynamic improvement was correlated to the endotoxin activity or other unknown factors.

Similarly, the Toraymyxin™ capacity to lower blood endotoxin levels and immunologic substances (IL-6) is not well understood, although the reported favourable effects on haemodynamics.

This pilot study aims to evaluate these two different blood purification treatments in terms of endotoxin activity and cytokines removal.

Patients will be followed-up during three days to collect parameters such as catecholamine support, hemodynamic parameters, SOFA score, lactate and procalcitonin which are parameters usually collected in septic shock. The survival rate at day 28 will be collected as well.

## **6 Objectives and endpoints of the clinical investigation**

### **6.1 Hypothesis and primary objective**

The primary objective of the study is to evaluate the endotoxin activity and removal with two extracorporeal blood purification treatments in septic shock patients.

### **6.2 Secondary objectives**

The secondary objectives of the study comprise the effects of the two blood purification treatments on cytokine and HMGB-1 removal, haemodynamics, safety, and outcome.

### **6.3 Primary endpoint**

The study primary endpoint is the measurement of the endotoxin activity 72 hours after treatment initiation.

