| Diagnosis and Inclusion Criteria: | 
 
Patients with septic shock, defined as: persistent catecholamine dependency with a vasopressor index > 3 after fluid resuscitation with at least 30ml/kg/KG prior to time of randomisation, and at least ONE of the following criteria: metabolic acidosis, neurologic dysfunction (GCS ≤ 14), renal dysfunction (RIFLE Classification: staging Injury or Failure) or hepatic dysfunction (Transaminase ≥ twice upper limit of normal).
 
Male and Female patients ≥18 years
 
Endotoxin levels ≥0.6 IU EAA within 24h from the time of suspected septic shock. If the first Endotoxin level is <math>0.4 \leq 0.6</math> IU EAA, the measurement should be repeated 2 -3 times within the screening period of 24 hours..
 
                                                                                               |
| Exclusion Criteria:               | 
 
Contraindications on ethical grounds
 
Endotoxin levels <0.6 IU EAA
 
Pregnancy or breast feeding
 
Neutropenia (circulating neutrophils <500/μl)
 
Immune-suppressive therapy or Steroid medication ≥30mg/d Prednisone Equivalent
 
Use of Vasopressin (Pitressin )
 
Organ transplantation within the last 12 months
 
Terminally ill patients classified as “do not resuscitate”
 
Have active bleeding or are at increased risk for bleeding, defined as platelets count after substitution >30 G/L; INR >4; and at least Substitution of more than 2 erythrocyte concentrate within 6 hours
 
History of sensitivity to polymyxin B or to anticoagulant (heparin) HIT or allergy to heparin
 
Need for extracorporeal membrane oxygenation (ECMO)
 
 |

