### **7.4 Study population**

#### **7.4.1 Inclusion Criteria**

The following inclusion criteria should be fulfilled at the time of enrollment within 24h of suspected septic shock.

Patients with septic shock, defined as: persistent catecholamine dependency with a vasopressor index > 3 after fluid resuscitation with at least 30ml/kg of i.v. fluid administered

prior to time of randomization, and at least ONE of the following criteria: metabolic acidosis, neurologic dysfunction (GCS  $\leq 14$ ), renal dysfunction, (RIFLE Class Injury or Failure), or hepatic dysfunction (Transaminases  $\geq$  twice upper limit of normal).

- Male and Female patients  $\geq 18$  years
- Endotoxin levels  $\geq 0.6$  IU within 24h from the time of suspected septic shock. If the first Endotoxin level is  $\geq 0.4 \leq 0.6$  IU EAA, the measurement should be repeated 2-3 times within the screening period of 24 hours.

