## **7.8.2 Sampling schedule**

### **7.8.2.1 Endotoxin measurements**

Endotoxin activity (EAA) will routinely be measured for patients admitted to the ICU if the diagnosis of Septic Shock is considered. Is the EAA level above the cut off threshold value 0.6 an evaluation for the study inclusion will be done (the result can be used for screening and enrolment (V1)). Furthermore the EAA will be measured at treatment start (V2), 24 hours after treatment initiation (V3), 48 hours after treatment initiation (V4), and 72 hours (V5) after treatment initiation (see treatment schedule p. 8). Blood samples will be obtained through an arterial line.

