## **13 Statistical considerations**

As mentioned, the endotoxin activity is not well described in the literature, which makes a sample calculation difficult. Therefore, this trial was designed as a pilot study analysing 30 patients in order to collect data enabling an accurate design of future investigations. Dependent and independent continuous variables will be compared using Wilcoxon and Mann-Whitney, respectively. In cases of serial measures repeated measures statistics will be applied. For multiple comparisons overall tests will be used: ANOVA for continuous variables and Kruskal-Wallis tests for ordinal scaled variables. Categorical data will be compared using Fisher's exact and  $\chi^2$  test. The normal distribution of study variables will be confirmed using Kolmogorov-Smirnov test. A P value < 0.05 will be considered statistically significant. To obtain adjusted differences in outcomes for the two study populations, logistic regression will be performed to control for factors or confounders that are significantly different ( $p < 0.05$ ) between compared groups. Data will be analysed using the Statistical Package for Social Sciences (SPSS Windows, version 19.0; SPSS Inc., Chicago, IL).

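### The primary T72 endotoxin activity comparison is not adjusted for the treatment-start value already collected, and the only adjustment rule stated does not fit it

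*Protocol*

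**What the plan says.** The objective in protocol section 6.1 is to "evaluate the endotoxin activity and removal with two extracorporeal blood purification treatments". The endpoint in section 6.3 is a single level: "The study primary endpoint is the measurement of the endotoxin activity 72 hours after treatment initiation". It is neither a change nor a baseline-adjusted value.

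Section 13 does not say which test is primary. For continuous variables it states: "Dependent and independent continuous variables will be compared using Wilcoxon and Mann-Whitney, respectively". It adds ANOVA or Kruskal-Wallis for overall tests and unnamed repeated-measures statistics for serial data. The one provision for adjustment is logistic regression on factors found to differ at p < 0.05, described for two study populations although the trial has three arms.

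A treatment-start value exists. Section 7.8.2.1 says: "Furthermore the EAA will be measured at treatment start (V2), 24 hours after treatment initiation (V3"), and then lists 48 and 72 hours. The same section lets the routine EAA serve as the screening value (V1).

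Entry is selected on the same variable. The synopsis requires "Endotoxin levels ≥0.6 IU EAA within 24h from the time of suspected septic shock". Under section 7.4.1, if the first value lies between 0.4 and 0.6, "the measurement should be repeated 2-3 times within the screening period of 24 hours". Section 7.7 plans to analyse 10 patients per group.

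**The concern.** With 10 patients per arm, sizeable chance differences in starting EAA are likely, and an unadjusted T72 comparison carries them into the result. The information that would remove them is already being collected. As worded, section 13 either leaves the primary comparison unadjusted or makes adjustment depend on a baseline significance test, followed by a model for a binary outcome.

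A second matter concerns baseline. Patients enter because an EAA reading was high, so later readings tend to be lower without any treatment. Section 13 plans paired Wilcoxon tests and no section says whether V1 or V2 is the baseline for EAA. A within-arm fall measured from V1 could be taken for removal by the device.

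At stake are the precision of the arm contrast and the usefulness of the pilot, whose stated purpose is to supply data for designing later trials.

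**Working it through.** **Inputs from the protocol.** 30 patients, 10 per group (sections 13 and 7.7); significance level 0.05, taken as two-sided; EAA at V2, 24, 48 and 72 h; entry at EAA ≥ 0.6 with 2–3 repeats only after a first value of 0.4–0.6; assay results of 0.2 or more accepted if the CV is below 15% (section 7.8.3.1). There is no power calculation to reproduce; 3 × 10 = 30 agrees.

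**Assumed.** 80% power and the V2–T72 correlation ρ, because the protocol gives no EAA mean, SD or correlation.

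**Detectable difference.** The standard error of a difference between two arms is SD × √(2/10) = 0.447 SD. Solving the noncentral t for 80% power:
- unadjusted, variance pooled over three arms (30 − 3 = 27 df): 1.30 SD
- unadjusted, two arms only (18 df): 1.32 SD
- adjusted for V2 (26 df): 1.30 × √(1 − ρ²)

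| ρ | 1 − ρ² | Detectable difference (SD) | Equivalent sample size, 1/(1 − ρ²) |
|---|---|---|---|
| 0.15 | 0.98 | 1.29 | 1.02 |
| 0.30 | 0.91 | 1.24 | 1.10 |
| 0.50 | 0.75 | 1.13 | 1.33 |
| 0.57 | 0.675 | 1.07 | 1.48 |

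These figures take V2 as balanced. Allowing for average chance imbalance multiplies the adjusted variance by 1 + 1/(27 − 2) = 1.04, so the differences by √1.04 = 1.02. At ρ = 0.15 that gives 1.29 × 1.02 ≈ 1.31 SD, no better than unadjusted. Break-even is where (1 − ρ²) × 1.04 ≈ 1, that is ρ ≈ 0.2.

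**Which correlations are plausible.** The entry cut-off narrows the baseline range and so lowers ρ. Two simulations of the entry rule, both on assumed EAA distributions, give the range among enrolled patients:
- Assay noise only, true EAA constant to 72 h (mean 0.45–0.55, SD 0.12–0.15, CV 10–15%): ρ = 0.39–0.67.
- With biological change (mean 0.4–0.6, SD 0.15–0.20, screening–V2 correlation 0.7–0.9, screening–T72 correlation 0.3–0.7): ρ = 0.14–0.57.

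A value of 0.7 lies above both.

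**Chance imbalance.** The difference in mean V2 between two arms has SD 0.447 in units of the V2 SD. The probability that it exceeds 0.5 SD in either direction is 2 × [1 − Φ(0.5/0.447)] = 26%. Such a gap shifts the expected unadjusted T72 difference by 0.5ρ: 0.15 SD at ρ = 0.3 and about 0.29 SD at ρ = 0.57. The p < 0.05 rule would not pick it up, since it needs an observed gap of about 2.05 × 0.447 = 0.92 SD.

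**Regression to the mean, no treatment effect.**

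| Model | Baseline | Mean fall (EAA units) | Paired Wilcoxon, n = 10, p < 0.05 |
|---|---|---|---|
| Assay noise only | V1 | 0.03–0.09 | 19–61% |
| Assay noise only | V2 | 0.00 | about 5% |
| Biological change | V1 | 0.05–0.21 | 22–55% |
| Biological change | V2 | 0.00–0.13 | 8–24% |

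The last column for biological change covers four scenarios. Selection acts before randomisation, so the expected fall is the same in every arm and cancels in the contrast with SOC.

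**The case against.** The best defence is that section 13 applies repeated-measures statistics to serial data, and EAA is serial. The primary test is not named, and model and covariate could sit in an analysis plan that is not shown. That stands against any claim that the protocol rules out baseline adjustment. It does not rescue the rule that is written down. If the logistic sentence is meant for binary outcomes only, no adjustment at all is stated for the primary endpoint. If it is meant generally, it cannot be applied to a continuous EAA.

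It is also fair that this is a pilot without a power claim, so detectable differences carry limited weight, and that the gain may be small. Both are accepted.

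Three stronger readings are tempting, and the documents do not support them:
- A reader might infer that selection on high EAA biases the primary comparison. It does not: there is a concurrent randomised SOC arm.
- A reader might infer that the planned within-arm tests will mostly give false positives. The high rates arise only from V1, which the protocol never names as baseline. From V2 they are nominal under assay noise alone and 8–24% with biological change. Nor does every patient enter after repeat testing; it applies only when the first value is 0.4–0.6.
- A reader might infer that T72 is the wrong time, since it falls 24 h after oXiris ends (72 − 48) and about 46 h after the second Toraymyxin session (72 − 26). The timings are right, but baseline adjustment does not address them, and this point keeps T72.

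**Conclusion.** The point holds as a low-cost improvement. The primary endpoint is one raw T72 value, the only adjustment rule stated does not suit it, and the natural covariate is already measured. Adjustment lowers the detectable difference from 1.30 SD to between about 1.29 and 1.07 SD for correlations of 0.15 to 0.57. That ranges from no real gain (below ρ ≈ 0.2) to the equivalent of roughly half as many patients again. It also removes imbalance of a size that has a 26% chance of arising between any two arms and that the p < 0.05 trigger would miss.

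A fall from V1 is partly regression to the mean and should not be read as removal. The randomised contrast with SOC is unaffected. Every magnitude rests on assumed EAA parameters.

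**What to change.** In section 13, or by reference from it:
- Make the primary between-arm analysis T72 EAA adjusted for V2 EAA, by ANCOVA or by a mixed model of the 24, 48 and 72 h values with arm, time, arm-by-time and V2 as covariate.
- Report the oXiris–SOC and Toraymyxin–SOC differences at T72 with 95% CIs, and the residual SD with its CI. With 26 df the limits are √(26/χ²), about 0.79 and 1.37 times the estimate, which is what a later trial needs for planning.
- Drop the logistic-regression rule for this endpoint and fix the covariate in advance, whatever the baseline test shows.
- State that V2, not the V1 qualifying value, is baseline, and that within-arm changes are descriptive.
- Add a rank-based sensitivity analysis that adjusts for V2, such as rank ANCOVA. A simple change from V2 is a poor substitute: its variance is 2(1 − ρ) times that of raw T72, which is larger whenever ρ < 0.5 (1.4 times at ρ = 0.3).

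The cost is wording only; every sample is already scheduled. The price is reliance on model assumptions with 30 patients, which the rank-based analysis covers.
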